## Abstract

Background. Despite ongoing treatment advancements in chronic heart failure (HF), mortality and readmission rates remain high for patients hospitalized for decompensated acute HF. These patients represent a distinct HF group, which requires emergent echocardiographic evaluation in an attempt to provide optimal and individualized acute care. The role of serial advanced echocardiographic assessment in acute HF for risk stratification and treatment guidance has not been thoroughly explored. Methods. The “Beyond Myo-HF Study” is a prospective, non-interventional cohort trial designed to enroll acutely admitted patients with symptoms and/or signs of HF. The aim of this study is to investigate whether intrahospital changes of conventional and novel echocardiographic indices of myocardial function and congestion-related markers can predict early mortality, late mortality, and HF rehospitalization. As per the protocol, all patients undergo a pair of state-of-the-art echocardiographic assessments, with a rigorous protocol including speckle tracking analysis of all cardiac chambers and myocardial work analysis for the left and right ventricle, upon admission and pre-discharge. Their laboratory profile is captured at those two time-points, and their therapeutic management is recorded. Patients will be followed-up for a median period of 12 months after enrollment. Conclusions. The “Beyond Myo-HF” study is an ongoing, prospective trial aspiring to provide deep insight into the pathophysiology of acute HF, to enlighten the reverse cardiac functional and anatomical remodeling during hospitalization, and to recognize echocardiographic patterns capable of predicting adverse outcomes during and post decompensation of acute HF.

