## 1. Introduction

Hospitalized patients with acute heart failure (HF) represent an understudied, distinct group of patients which has mainly been characterized through registries [1]. These patients largely differ from stable outpatients with chronic HF in terms of clinical course, and continue to suffer very poor prognosis; they have an estimated mortality and readmission rate of 15% and 30%, respectively, between the first and second month post discharge [2]. In this regard, it is of paramount importance to identify vulnerable subjects in order to intensify their follow-up and outpatient care. Suboptimal echocardiographic improvement in response to acute HF treatment may represent a red flag but current literature is scarce.

In acute decompensated HF, intensive therapy aims to lessen intracardiac pressure and central venous congestion [3], which is expressed as an improvement of the circulatory volume-dependent echocardiographic parameters, mainly evidenced through reverse remodeling of the thin-walled right ventricle (RV). It has been suggested that improvement of RV function surrogates such as tricuspid annular plane systolic excursion (TAPSE) and right ventricular–pulmonary artery (RV–PA) coupling is of prognostic relevance [4]. However, TAPSE has obvious limitations as it poorly reflects overall contractility of the RV [5], and it has been surpassed by speckle tracking echocardiography with longitudinal strain, which is sensitive in detecting dynamic improvement in RV mechanics [6].

Longitudinal strain does not integrate ventricular dyssynchrony into its quantitative output and does not account for the afterload, which is subject to considerable alterations with the intensive acute HF medical therapy particularly for the RV. Myocardial work is a non-invasively derived index of myocardial function that accounts both for ventricular dyssynchrony and afterload [7]. Although originally dedicated for the left ventricle, this method has recently been evaluated for the RV and has shown significant correlation with invasively measured RV stoke volume [8]. Nonetheless, its prognostic implications in the acute HF setting have not been comprehensively investigated so far.

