Before each TTE study, heart rate and brachial blood pressure using a conventional sphygmomanometer are recorded. Additionally, height and weight of each participant are recorded and utilized to determine body mass index and body surface area in accordance with the Dubois formula [9]. Informed written consent is obtained from all participants prior to study enrollment. All patients undergo standard of care acute HF management, as dictated by their clinical presentation, the practice of the hospital, and most updated guidelines [10]. The investigation conforms with the principles outlined in the Declaration of Helsinki (2013 Amendment), and the study protocol was approved by the Ethics Committee of the School of Medicine of Aristotle University of Thessaloniki (Approval number: 19/2022, Date of approval: 10 November 2022).

In accordance with the guideline-recommended HF definitions [10], HF patients are classified on the basis of their left ventricular ejection fraction (LVEF), as this is calculated from the admission TTE study. Those are patients with (i) heart failure with reduced ejection fraction (LVEF ≤ 40%), (ii) heart failure with mildly reduced ejection fraction (LVEF = 41–49%), and (iii) heart failure with preserved ejection fraction (LVEF ≥ 50%). In addition, patient are classified as new-onset or chronic HF, on the basis of a previously documented HF hospitalization. The trend of their echocardiographic profile during hospitalization is recorded to identify predictors of early and late mortality, and HF rehospitalization at follow-up. Follow-up data are collected regularly by independent physicians via in-person or telephonic interviews. All deaths are ascertained by searching in the Greek web-based national health insurance system. Other clinical outcomes, apart from death, are identified either through hospital reports or by telephone contact.

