### 3.6. Statistical Analysis

Baseline clinical and echocardiographic characteristics of each group will be examined and compared using the chi-square test for categorical variables and the two-sided Student’s *t*-test or the analysis of variance (ANOVA) test for continuous variables depending on the number of groups. Categorical variables will be represented by frequencies and percentages (%) and continuous variables will be summarized by mean ± standard deviation. Comparison of changes in echocardiographic indexes between admission and discharge will be performed using the paired *t*-test or Wilcoxon signed rank test according to the normality of distribution.

Univariate and multivariate logistic regression analysis and Cox regression analysis will be performed to identify independent predictors of outcome at follow-up. Only covariates that are significantly associated with the endpoint at univariate analysis will be included in multivariate models. The sensitivity and specificity of resulting echocardiographic parameters for the prediction of early mortality, late mortality, and rehospitalization will be evaluated with receiver operating characteristic curves. To assess the potential additive prognostic value of novel imaging biomarkers over baseline models, the additional increase of the chi-square value will be assessed using the likelihood ratio test. A time-to-event analysis will be performed according to the Kaplan–Meier method to assess whether groups of patients with specific echocardiographic patterns are associated with better or worse clinical prognosis. Event rates will be compared by the long-rank test. A two-tailed *p* value of 0.05 will be considered the significance threshold for all statistical tests. All outcomes will be reported with 95% confidence intervals. Data management and statistical analyses will be conducted using SPSS software, version 26 (IBM SPSS Statistics) and R version 3.4.4 (R Foundation for Statistical Computing, Vienna, Austria).

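### Section 3.6 has no method that accounts for death before HF rehospitalization; if Kaplan–Meier is used for that outcome with deaths censored, readmission risk is overstated, most in the groups that die most

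*Protocol article*

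**What the plan says.** The Abstract sets out to learn whether in-hospital echocardiographic changes "can predict early mortality, late mortality, and HF rehospitalization". The Study Design and Population section repeats the three outcomes: the aim is to "identify predictors of early and late mortality, and HF rehospitalization at follow-up". Rehospitalization is listed beside mortality each time, and no composite of the two is defined.

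Section 3.6 names these outcome methods:

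- Regression: "Univariate and multivariate logistic regression analysis and Cox regression analysis will be performed to identify independent predictors of outcome at follow-up".
- Discrimination: sensitivity and specificity "for the prediction of early mortality, late mortality, and rehospitalization will be evaluated with receiver operating characteristic curves".
- Time to event: "A time-to-event analysis will be performed according to the Kaplan–Meier method". The purpose given for this analysis is to compare prognosis between patient groups defined by their echocardiographic pattern; no endpoint is named.
- Group comparison: "Event rates will be compared by the long-rank test" (a misprint for log-rank).

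No section says what happens in any of these analyses to a patient who dies without having been readmitted. On background risk, the Introduction says of these patients that "they have an estimated mortality and readmission rate of 15% and 30%, respectively, between the first and second month post discharge". Median follow-up is 12 months (Abstract).

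**The concern.** A patient who dies cannot later be readmitted, so death is a competing event for rehospitalization. By the Introduction's own figures it is half as frequent as readmission. With the listed tools, and without a composite, such a patient has to be censored (Kaplan–Meier, Cox), counted as event-free (logistic, ROC) or left out. These choices answer different questions, and the plan does not choose among them.

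Two results are at stake. The first is the absolute readmission risk read off a Kaplan–Meier curve: with deaths censored, it estimates readmission as if nobody died. The second is the ROC result: a marker of severe disease is likely to predict death too, and the area under the curve (AUC) then depends on where the deaths are placed. Both matter here because section 4 aims to profile patients prone to death and to early readmission alike, so the groups compared are expected to differ in mortality.

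**Working it through.** The article gives no power calculation or event count, so there is no figure of its own to reproduce. The check uses constant cause-specific hazards over the period: h_r for readmission and h_d for death.

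- Kaplan–Meier with deaths censored: 1−KM = 1 − exp(−h_r).
- Actual readmission risk: CIF = h_r/(h_r+h_d) × [1 − exp(−(h_r+h_d))].

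**At the document's figures (30% readmission, 15% death).** The 15% can be read in two ways.

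- As the death risk if readmission did not intervene: h_d = −ln(0.85) = 0.1625. CIF = 0.30 then requires h_r = 0.3906 (check: 0.3906/0.5531 × [1 − exp(−0.5531)] = 0.300). 1−KM = 1 − exp(−0.3906) = 32.3%, an excess of 2.3 points.
- As death without prior readmission: h_r+h_d = −ln(1 − 0.30 − 0.15) = 0.598 and h_r = 0.598 × 0.30/0.45 = 0.399. 1−KM = 32.9%, an excess of 2.9 points.

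**At 12 months.** The document gives no 12-month rates. The rates below are assumptions, with death on the first reading. Entries are 1−KM minus CIF, in points.

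| Death risk | CIF 30% | CIF 40% | CIF 50% |
|---|---|---|---|
| 10% | 1.5 | 1.9 | 2.3 |
| 15% | 2.3 | 3.0 | 3.6 |
| 20% | 3.2 | 4.2 | 5.0 |
| 30% | 5.2 | 6.7 | 8.0 |
| 40% | 7.6 | 9.6 | 11.4 |

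**Two groups with the same readmission hazard, death 10% versus 40% (assumed).** With h_r = −ln(0.60), 1−KM is 40% in both groups. CIF is 38.1% and 32.0%. The excess is therefore 1.9 points in one group and 8.0 in the other.

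**Two groups with a readmission hazard ratio of 1.5, death 10% versus 40% (assumed).** 1−KM is 30.0% versus 41.4%, a gap of 11.4 points. CIF is 28.6% versus 33.2%, a gap of 4.6 points.

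**Log-rank test.** Simulation with 300 patients (150 per group), equal readmission hazards, death 10% versus 40%, deaths censored, 4,000 runs: type I error 4.9%. Unequal mortality does not disturb it as a test of the cause-specific hazard.

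**ROC.** Simulation with 200,000 patients and a normally distributed marker. The log hazard ratio for readmission is 0.5 per SD, and at the mean marker value the 12-month readmission risk is 35% and death risk 20%, each in the absence of the other event (all assumed).

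| Log hazard ratio for death per SD | AUC without death | Deaths as non-events | Deaths excluded |
|---|---|---|---|
| 0 | 0.67 | 0.66 | 0.67 |
| 0.5 | 0.67 | 0.63 | 0.68 |
| 1.0 | 0.67 | 0.60 | 0.69 |

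**The case against.** Four objections deserve an answer.

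1. *The Kaplan–Meier sentence does not name rehospitalization.* True. Its stated purpose is prognosis in general, so all-cause death or a composite is not excluded. Rehospitalization is one of only three outcomes, so its use there is a natural reading, but the point on 1−KM has to stay conditional. The ROC point does not depend on this, because that sentence names rehospitalization.

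2. *A condensed article may leave the handling of death to a fuller plan.* This also stands in part and lowers the severity. But section 3.6 is specific about its outcome methods, down to the likelihood ratio test for added markers, and none of those it fixes gives readmission risk in the presence of death.

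3. *A mortality difference does not make the comparison of readmission false.* A reader might infer that it does from groups with equal 40% readmission incidence and death without readmission of 10% versus 40%, where 1−KM reads 42.6% versus 55.3%, about 13 points apart. That inference fails. The example implies readmission hazards of 0.693 × 0.8 = 0.555 and 1.609 × 0.5 = 0.805, a ratio of 1.45. Patients still alive really are readmitted at different rates, and the log-rank test and Cox model would detect that correctly. The error lies only in reading the curves as actual risk.

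4. *Gray's test and the Fine–Gray model are not corrections of log-rank and Cox.* Correct. With equal readmission hazards, cumulative incidence differs (38.1% versus 32.0%) only because more patients die in one group. The two approaches answer different questions, and substituting one for the other is a choice of estimand. Likewise, counting the dead as not readmitted is what cumulative incidence itself does, so it is not wrong for absolute risk. It is a problem in an ROC analysis when the make-up of the comparison group is left unstated.

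**Conclusion.** The point holds in a limited form, as a should-fix. If Kaplan–Meier is applied to HF rehospitalization with deaths censored, 1−KM overstates actual readmission risk, and more so in groups with higher mortality: 2.3 to 2.9 points at the Introduction's rates, and 1.5 to 11.4 points for assumed 12-month death of 10 to 40% and readmission of 30 to 50%. The calculation assumes constant hazards. The early figure may be somewhat high, because some of the 15% may die after a readmission, and those deaths do not compete.

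A reader might go further and conclude that every listed method overstates readmission. The documents and the arithmetic do not support that. Log-rank and Cox results are valid for the cause-specific hazard. ROC with deaths pooled among event-free survivors moves the other way: AUC falls from 0.67 to between 0.63 and 0.60 when the marker also predicts death, and rises to 0.68 to 0.69 if deaths are excluded. The size of that shift rests on assumed marker effects; what is firm is that the AUC depends on a choice section 3.6 does not state.

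**What to change.** For HF rehospitalization, amend section 3.6 or the analysis plan as follows:

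- Report Aalen–Johansen cumulative incidence curves, with death before readmission as the competing event, instead of 1−KM.
- Keep the log-rank test and Cox regression, labelled as comparisons of the cause-specific hazard of readmission. Gray's test or a Fine–Gray model may be added as supplements, not replacements.
- Use a time-dependent ROC that handles death as a competing event, and state whether patients who die unreadmitted belong to the comparison group. State the same for logistic regression.
- Keep Kaplan–Meier for all-cause death and, if one is added, for a composite of death or first HF rehospitalization.

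The cost is a few sentences and a little extra analysis. Deaths are already ascertained through the national health insurance system (Study Design and Population), and R is already named in section 3.6. No new data or patients are needed.

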## 4. Discussion and Expected Results

The “Beyond Myo-HF Study” is an ongoing, prospective cohort trial of patients hospitalized for acute HF, aiming to elucidate the intrahospital echocardiographic changes and their prognostic value. By providing a comprehensive echocardiographic assessment at admission and discharge, it seeks to evaluate the acute haemodynamic changes and the subtle alterations in myocardial function by speckle tracking echocardiography, and ultimately profile subjects not responding to intensive acute HF therapy, prone to mortal events and early HF rehospitalization.

Only a few studies have described the echocardiographic changes of acute HF patients from admission to discharge [3,4,6]. Hullin et al. studied 176 AHF patients and demonstrated a significant decongestion-related improvement for mitral E wave velocity, E/e’ ratio, RV basal diameter, tricuspid regurgitation gradient, PASP, TAPSE/PASP, and inferior vena cava diameter across all LVEF groups [4]. In regard to parameters of LV systolic function, LVEF remained unchanged with decongestion while LV GLS improved, depicting an LV endomyocardial functional recovery at discharge [4]. Concerning RV function, subjects who demonstrated an increase of TAPSE and/or TAPSE/PASP with treatment had a significantly lower risk for death or cardiovascular readmission [4]. Akiyama et al. studied 77 patients with acute HF and described an improvement of E-wave deceleration time and inferior vena cava diameter for heart failure with reduced ejection fraction patients and an improvement of E/e’ for heart failure with preserved ejection fraction patients [3]. However, speckle tracking data were not provided and the prognostic implications of those changes were not evaluated [3]. Verhaert et al. studied 62 AHF patients, focusing on RV mechanics, and concluded that RV response to intensive medical therapy, indicated by improvement of RV GLS, conveyed better prognosis [6].

Both LV and RV potential functional recovery during hospitalization for acute HF is mainly detected by longitudinal strain of LV and RV, respectively, by applying speckle tracking echocardiography [4,6]. This parameter is more capable of tracking subtle intrinsic myocardial response to treatment compared to LVEF [18], and in an angle-independent manner compared to Doppler-derived indices of ventricular function. Although longitudinal strain evaluates the endomyocardial function and is not merely based on volumetric ventricular changes like RV fractional area change or LVEF [19], it is not completely independent of afterload. However, in acute HF the afterload of both LV and RV may change significantly during treatment with inotropes and heavy dosing of diuretics, while a reduction of blood pressure and pulmonary pressure is driven mainly by changes to the patient’s volume status and vascular resistance.

Especially for those on inotropes in the acute HF setting, suboptimal echocardiographic improvement of the intrinsic myocardial systolic properties to therapy may indicate limited myocardial reserve for the existent afterload [6]. In patients with coexistent significant mitral or tricuspid regurgitation, the longitudinal strain may be more sensitive for revealing myocardial functional improvement compared to volumetric assessment of the ventricular function [20], considering that the ventricle partly empties in a low-pressure cavity; of note, the grade of the regurgitation—especially if it is functional—is substantially dependent on the afterload. Thus, there is an unmet need to adjust the longitudinal strain for the ventricular afterload in acute HF patients, which is currently feasible by echocardiography-evaluated myocardial work indices [7].

In the current study, the response to acute HF therapy will be assessed, among others, by computation of non-invasive LV myocardial work parameters. Such novel indices are estimated via dedicated software by integrating speckle tracking LV GLS, blood pressure as an afterload estimate, and cardiac event timing to formulate a pressure–strain loop of the LV [7]. Accounting for dyssynchrony and afterload, LV global myocardial work has shown to provide incremental prognostic information over and above LV GLS and LVEF regarding all-cause mortality or HF hospitalization between subjects with heart failure with reduced ejection fraction [21]. Additionally, Hedwig et al. displayed that LV GWI and LV GCW could independently predict events among a group of advanced HF patients [22]. Only one study has assessed dynamic in-hospital changes of myocardial work indices for acute HF patients and observed improvement of GCW and GWI only for heart failure with reduced ejection fraction but not heart failure with preserved ejection fraction patients [23]. The prognostic implications of those intrahospital changes were not investigated in the aforementioned work [23].

The RV is a thin-walled cardiac chamber with low ventricular elastance, whose contractile properties are more susceptible to its loading environment, preload, and afterload, compared with the LV [24]. Those characteristics render the RV more vulnerable to acute changes in hemodynamic conditions and thus suited for serial echocardiographic assessment to identify response to intensive therapy and recovery after an acute HF episode [6]. Reducing peripheral congestion or pulmonary pressures would have a strong impact on RV size and function. RVMW, combining information on contractile function by stain analysis and on afterload assessed by PASP, is an echocardiographic parameter that could reflect alterations in response to acute treatment. This study aims to expand the current literature by investigating the intrahospital changes and prognostic significance of RV myocardial work in acute HF.

Functional tricuspid regurgitation is a very common valvular heart disease growing in parallel with the progression of HF [25]. Significant functional TR is associated with unfavorable natural history for patients with HF, as it leads to a vicious cycle of RV dilatation, arrhythmias, and RV failure when left untreated [26]. However, functional tricuspid regurgitation is a marker of congestion and its dynamic nature with improvement in response to medical therapy should be acknowledged. This improvement is theoretically driven by adverse RV remodeling with reduction of the RV afterload, the RV and tricuspid annular dimensions, attenuation of the tethering effects, and functional RV recovery. Among others, this study aims to identify the RV anatomical and functional profile of subjects who experience amelioration of tricuspid regurgitation grade in response to acute HF therapy, and explore if this profile is associated with better outcomes.

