## 2. Methods and Materials

### Study Design and Population

The “Beyond Myo-HF Study” (ClinicalTrials.gov Identifier: NCT05573997) is an investigator-initiated, prospective, non-interventional cohort trial involving patients with acute HF. A total of 300 consecutive patients acutely admitted to the Department of Cardiology of AHEPA University General Hospital, Thessaloniki, Greece with symptoms and/or signs of HF satisfying the inclusion criteria are enrolled in the present study. Eligibility criteria are described in Table 1.

Demographic characteristics and baseline medical history including a history of previous hospitalization for acute HF, primary etiology, and clinical presentation of hospitalization are recorded for all participants. Pharmacological and non-pharmacological therapeutic maneuvers during the acute phase of hospitalization, as well as medical therapy upon admission and discharge, are collected. A comprehensive transthoracic echocardiographic assessment (TTE) is performed at two different time-points during hospitalization. The first TTE is performed within 24 h from admission, and the second with 24 h pre-discharge, to capture the trajectory and net variations of all echocardiographic indices of interest. A cardiac computed tomography or cardiac magnetic resonance study will be routinely performed as required to investigate the primary HF cause for undiagnosed patients. In addition, patients’ laboratory results including complete blood count, biochemical control, inflammatory markers, coagulation mechanism control, hormonal control, N-terminal pro-B-type natriuretic peptide, and high sensitivity troponin T levels are collected upon admission and prior to discharge (Figure 1).

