### 3.2. Chamber Quantification Analysis

The size of all cardiac chambers is assessed in accordance with most current recommendations [11]. Two-dimensional and Doppler measurements are performed as recommended [11,12]. Simpson’s biplane method is utilized to calculate left ventricular ejection fraction (LVEF) and abnormal values of conventional left ventricular (LV) diastolic parameters are determined on the basis of recently established criteria [12]. All RV systolic function parameters including TAPSE, fractional area change, and systolic movement of the RV lateral wall (S’) are evaluated as per current guidelines [13]. RV fractional area change is calculated by the formula: Fractional Area Change = ([RV end-diastolic area − RV end-systolic area]/RV end-diastolic area) × 100%. TAPSE is measured by M-mode and S’ by pulse-wave tissue Doppler imaging (TDI) recordings of the lateral tricuspid annulus in an RV-focused view [13]. Estimated right atrial pressure is determined on the basis of the evaluation of inferior vena cava and its collapsibility [13]. Pulmonary artery systolic pressure (PASP) is derived from the tricuspid jet peak velocity and the estimated right atrial pressure using the modified Bernoulli equation [13]. An integrated approach is used to quantify the severity of valvular heart disease in line with the recommendations from the respective guidelines [14,15]. A scale ranging from 1 to 4 to define mitral regurgitation and tricuspid regurgitation severity is employed as suggested by recent published literature [15,16]: grade 1 indicates “mild”, 2 “moderate”, 3 “moderate-to-severe”, and 4 refers to “severe” mitral regurgitation or tricuspid regurgitation.

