## Figures and Tables

**Figure 1 diagnostics-13-01191-f001:**
[figure not shown]
Study design diagram. Serial echocardiographic and laboratory assessment will be performed in 300 consecutive patients admitted with acute heart failure, in order to identify predictors of early mortality, late mortality, and heart failure rehospitalization. Abbreviations: ACS, acute coronary syndrome; HFpEF, heart failure with preserved ejection fraction; HFrEF, heart failure with reduced ejection fraction.

**Table 1 diagnostics-13-01191-t001:** Inclusion and exclusion criteria of the “Beyond Myo-HF study”.

Inclusion Criteria	Exclusion Criteria
Symptoms and/or signs of heart failure Abnormal plasma concentration of N-terminal pro-B-type natriuretic peptide, measured within 24 h of admission Objective echocardiographic evidence of cardiac structural and/or functional abnormalities consistent with the presence of LV systolic dysfunction/diastolic dysfunction/raised LV filling pressures upon admission assessment Adult patients	Symptoms and/or signs of HF secondary to congenital heart disease, infective endocarditis, pericardial disease, and history of recent cardiac surgery (<1 month); pulmonary circulation pathologies such as I, IV, V pulmonary hypertension Patients receiving maintenance hemodialysis or peritoneal dialysis Severe liver insufficiency Patients with active malignancy and/or life expectancy <1 year because of comorbidities Heart transplantation Poor echocardigraphic acoustic windows precluding reliable assessment and/or analysis Patients not providing informed written consent to participate in the study

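### Admission-to-discharge change is tested unadjusted and read as treatment response, so a first scan on an inotrope and a second off it can pass for lack of improvement; coding support at each scan is a cheap safeguard

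*Protocol article*

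**What the plan says.** **Timing.** Study Design and Population ties the two scans to the clock only: "The first TTE is performed within 24 h from admission, and the second with 24 h pre-discharge". No condition is set on the treatment running at the time.

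**What is recorded.** The same section states: "Before each TTE study, heart rate and brachial blood pressure using a conventional sphygmomanometer are recorded". Height and weight are also taken. On treatment it states: "Pharmacological and non-pharmacological therapeutic maneuvers during the acute phase of hospitalization, as well as medical therapy upon admission and discharge, are collected". It does not link treatment to the time of the scan.

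**Who is eligible.** Table 1 does not exclude patients on inotropes or other circulatory or ventilatory support. Its imaging exclusion is "Poor echocardigraphic acoustic windows precluding reliable assessment and/or analysis".

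**What is expected.** The Discussion says that "in acute HF the afterload of both LV and RV may change significantly during treatment with inotropes and heavy dosing of diuretics", so inotrope use is foreseen in this setting.

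**Analysis.** Section 3.6 specifies a paired t-test or Wilcoxon signed rank test for change. It admits a covariate to a multivariable outcome model only if it is significant on its own.

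**Interpretation.** Aim (iv) at the end of the Introduction asks whether too little improvement by discharge, understood as response to acute treatment, goes with worse prognosis. The opening of the Discussion speaks of profiling patients who do not respond to intensive therapy. Further on, the Discussion ties poor improvement to limited reserve: "Especially for those on inotropes in the acute HF setting, suboptimal echocardiographic improvement of the intrinsic myocardial systolic properties to therapy may indicate limited myocardial".

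**The concern.** An inotrope acts on the quantities being compared: strain, TAPSE, S' and myocardial work. If it is running at the first scan and stopped before the second, the first reading is stimulated and the second is not. The difference then contains recovery and drug withdrawal, in opposite directions, and the patient can be counted as not improving even though the myocardium has recovered.

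Myocardial work does not remove the problem. It brings pressure into the index, but it does not separate drug-stimulated contraction from intrinsic function.

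Aim (iv) is where this matters. Patients who needed an inotrope are plausibly at higher risk of dying. If they are also over-represented among apparent non-responders, part of the link between poor echocardiographic change and poor outcome would reflect having needed support. The stated covariate rule gives no assurance that support is adjusted for. A confounder can matter without reaching univariate significance, particularly if supported patients or events are few.

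**Working it through.** The article states no effect size, power or inotrope frequency, so there is no figure to reproduce. What follows is an illustration.

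**Inputs from the document:** n = 300 (treated as 300 complete pairs); two-sided alpha 0.05.

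**Assumed inputs (not in the document):**
- f, the share of pairs with support at the first scan only: 5% to 30%.
- d, the downward shift in measured change caused by withdrawal: 0.3 to 0.8 SD of change.
- True mean improvement: 0.5 SD where responder status is considered, with non-response defined as change ≤ 0.
- k, the event risk of supported relative to other patients: 2 or 3.

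**Step 1. Sensitivity of the paired test.** Shift detectable with 80% power = (1.960 + 0.842)/√300 = 0.162 SD. Small biases are therefore visible to this test.

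**Step 2. Bias in mean change** = f × d. Low end: 0.05 × 0.3 = 0.015 SD. Middle: 0.20 × 0.5 = 0.10 SD. High end: 0.30 × 0.8 = 0.24 SD.

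**Step 3. Chance of a significant paired test when there is no true change.** The SD of the mixture is √(1 + f(1−f)d²). For f = 0.20 and d = 0.5 it is √1.04 = 1.020, so the standardised shift is 0.10 × √300/1.020 = 1.70. The probability is Φ(1.70 − 1.96) plus a negligible lower tail, about 0.40. The low and high ends give 0.058 and 0.97.

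**Step 4. Apparent non-response at a true improvement of 0.5 SD.** Unaffected pairs: Φ(−0.5) = 0.309. Affected pairs: Φ(−(0.5 − d)), which is 0.421, 0.500 and 0.618 for d = 0.3, 0.5 and 0.8.

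**Step 5. Supported patients among apparent non-responders and responders.** Writing s for the affected rate from Step 4, the share among non-responders is f·s/[f·s + (1−f)·0.309]. Among responders it is f(1−s)/[f(1−s) + (1−f)·0.691].

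**Step 6. Spurious association with outcome.** Suppose that, within each support group, change has no relation to outcome. The crude risk ratio of non-responders to responders is then [1 + (k−1) × share in non-responders]/[1 + (k−1) × share in responders].

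| f, d | Share in non-responders | Share in responders | Risk ratio, k = 2 | Risk ratio, k = 3 |
|---|---|---|---|---|
| 5%, 0.3 SD | 0.067 | 0.042 | 1.02 | 1.05 |
| 20%, 0.5 SD | 0.288 | 0.153 | 1.12 | 1.21 |
| 30%, 0.8 SD | 0.462 | 0.191 | 1.23 | 1.39 |

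For the middle row with k = 2: 1.288/1.153 = 1.12.

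The false association is trivial at the low end and moderate at the high end. In the scenarios shown, support alone does not produce a strong one.

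**The case against.** **The Discussion sentence on inotropes is background.** It rests on a cited study, is hedged, ends by referring to the prevailing afterload, and is not an analysis rule. A reader might infer that the plan has decided to read withdrawal of support as myocardial failure. The document does not say so. The point rests on the unadjusted comparison, the covariate rule and aim (iv).

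**Treatment is collected.** This covers the acute phase and also medical therapy on admission and at discharge, close to the two scans. This stands: the information may already be in hand, and the full protocol or the scan form, which are not shown, may record support per scan. The absence of a form field from an article is no fault. What remains is that the stated analysis makes no use of the information.

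**The Limitations partly concede it.** They say that linking echocardiographic change to treatment is difficult because treatment can vary daily. This stands in part, but no analytic remedy follows.

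**Ventilation and mechanical support are never named.** A reader might infer a second artefact through right atrial pressure: "Estimated right atrial pressure is determined on the basis of the evaluation of inferior vena cava and its collapsibility", which means something different under positive pressure. By the formulas in sections 3.2 and 3.5, an error e in right atrial pressure does pass in full to PASP and PAMP, and to PADP, since 1.5 × (e − e/3) = e. But the article does not show that such patients are scanned. The consent rule ("Informed written consent is obtained from all participants prior to study enrollment") and the acoustic-window exclusion may keep some out. An inflated admission pressure that later falls would look like improvement, the opposite of the inotrope effect. The two cannot be added into one bias.

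**The sickest patients may not contribute.** Patients who die in hospital normally have no pre-discharge scan and so supply no pair. This stands and limits the effect on aim (iv).

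**The screening rule may work.** If support predicts death strongly and is offered as a covariate, it would tend to enter the model. True, but adjustment then depends on a significance test.

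**Conclusion.** The point holds as a cheap improvement to the analysis and is not an error in the design. The plan compares raw change between scans that may be taken in different support states, does not guarantee adjustment, and reads poor change as poor response. On/off pairs can therefore be misclassified as non-response.

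The size is unknown because the document gives neither the share of such pairs nor the effect of withdrawal. Under the assumed ranges it runs from negligible (0.015 SD bias; spurious risk ratio 1.02 at k = 2) to material (0.24 SD; 1.23 at k = 2, 1.39 at k = 3). The middle case is 0.10 SD and a ratio of 1.12 at k = 2.

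A reader might go further and infer that the aim (iv) result would simply be produced by having needed support. The documents do not support that: inotrope frequency is not given, treatment data are collected, the ventilation mechanism is inferred and may act the other way, and in-hospital deaths drop out of the paired data.

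**What to change.** 1. From the treatment data already collected, or from the drug chart, code for each TTE whether an inotrope or vasopressor was running, and whether any ventilatory or mechanical support was in use.
2. Report the number of on/on, on/off, off/on and off/off pairs. This replaces the assumed f with an observed figure and shows at once whether the issue matters.
3. Keep all pairs in the main analysis. Restricting it to same-state pairs would remove higher-risk patients from a consecutive cohort.
4. In section 3.6, add that support at the first scan enters the models relating echocardiographic change to outcome whatever its univariate p value.
5. Add a sensitivity analysis limited to pairs in the same support state, with on/off pairs described separately.

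**Cost:** a small chart-abstraction task, one more model term, and a smaller sample in the sensitivity analysis. The study is ongoing, so this is still feasible, and nothing in patient care changes.
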